**Visit at M3**

*For all patients*

- Clinical examination
  - Date of examination
  - Age
  - Height
  - weight
  - Pulmonary function test (FVC, FEV1)
  - Pulmonary infections
  - clinical examination (respiratory, digestive, cardiovascular, neurological, skin condition , general condition)
- Assessment of pain (mean VAS and number of days in the previous month) for :
  - Neck and trapezes pain
  - Chest and back pain
  - Headache
- Other pain (location, VAS, start date, end date, medication)
- Taking analgesics, NSAIDs , muscle relaxants or antidepressants over the last month (dosage, route , start date, end date , indication)
- Osteopathic results (assessed area, severity, major or specific somatic dysfunction)
- Self-administered questionnaire of quality of life, specific for cystic fibrosis
  - physical functioning
  - energy/well-being
  - body image
  - respiratory symptoms

**Visits at M4 and M5**

*For patients in groups 1 and 2 (groups with osteopathic treatment)*

Same data as for visits 1 and 2

**Visit at M6**

*For all patients*

- Same data as for visit 3
- Satisfaction questionnaire

**5. Declaration of adverse events and severe adverse events**

### Non serious adverse events:

Any adverse event observed during and following the research will be reported in the CRF in the section provided for this purpose. The event may be a symptom, a diagnosis or the result of an additional exam considered significant. All clinical and paraclinical evidence that best describe the corresponding event should be reported.

### Serious adverse events (SAE):

The investigator should inform in real time, the sponsor AP-HP, of any serious adverse event.

The investigator completes the form of SAE reporting of the CRF and sends it by [contact]) to DRCD on behalf of the project manager in charge of the research, within 48 hours (if possible after a call at [name] in case of death or unexpected life-threatening event). The investigator must also inform the Paris Centre Clinical Unit Centre in charge of the research of the occurrence of SAEs.

For each serious adverse event, the investigator shall issue a medical opinion on the possible relationship between the occurrence of the event and the protocol.

Any safety data or any developments that could significantly change the assessment of the benefits and risks of the research, or that could lead to consider amendments regarding the conduct of the research, will be provided by the sponsor to the competent authorities, the IRB and the investigators of the study

# 6. Statistical analysis plan

## 6.1. Definition of endpoints

### 6.1.1 Primary endpoint

For the primary analysis, a composite endpoint will be used. For each patient the following two parameters will be averaged:

1) The evaluation of chest and back pain on the previous month (VAS 0 to 10)

2) (The number of days in the month when the patient experienced chest back pain / Total days of the previous month) *10 (score from 0 to 10)

### 6.1.2 Secondary endpoints

Secondary endpoints are:

- The mean between (the evaluation of neck and trapezus pain on the previous month) and (the number of days in the month when the patient experienced neck and trapezus pain) / (total days of the previous month) *10.
- The mean between (the evaluation of headache on the previous month) and (the number of days in the month when the patient experienced headache) / (total days of the previous month) *10.
- For quality of life, each of the 4 studied scores (physical functioning, energy / well-being, body image and respiratory symptoms) will be standardized (values ranging from 0 to 100). The average of these four standardized scores will be used as an endpoint.

## 6.2. Number of subjects required

Total number of patients planned: n = 32

Number of patients receiving general osteopathic treatment (group 1): n=16

Number of patients receiving specific osteopathic treatment (sham treatment)(group 2 ): n=8

Number of patients for the untreated control group (group 3): n = 8

We recall that this is a pilot study, in the case of a rare disease, "justifying" the small number of patients planned. However, the number of subjects should make it possible to have 80% power to demonstrate a difference of about one standard deviation of the mean VAS for pain in the group treated by general osteopathy versus the two other groups (treated by specific osteopathy or untreated (performing bilateral test with a significance level of 5%).

## 6.3. Statistical analysis

### 6.3.1 Population analysis

Only the intent-to-treat (ITT) population will be analyzed. The ITT population was defined as all randomized subjects. They will be analyzed in the group they were randomized regardless of the treatment actually received, regardless of their fate in the study.

**6.3.2 Descriptive statistics**

For the data collected at the inclusion visit, a descriptive analysis will be performed per group. Qualitative variables are described by their number, percentage and missing data by response category. Quantitative variables are described by their value, median and interquartile range [25th percentile, 75th percentile].

For osteopathic assessment, prevalence, severity index and the "burden" will be calculated for each anatomical region. The prevalence is calculated for each degree of severity (mild, moderate, severe) of the studied area and globally.

Example of descriptive analysis for an osteopathic assessment (n=1331 patients)^[[1]](#footnote-1)^ :

|  | Prevalence, n (%) | | | |  |  |
| --- | --- | --- | --- | --- | --- | --- |
| Anatomic area | Mild | Moderate | Severe | Total | Severity index | Burden |
| Head | 20 (49) | 19 (46) | 2 (5) | 41 (3.1) | 1.56^a^ | 4.8^b^ |

^a^(20x1 + 19x2 + 2x3)/41 = 1.56, ^b^3.1x1.56 = 4.8

No statistical test comparing groups from randomization will be performed at baseline.

### 6.3.3 Main analysis

The comparison will be made between the "general osteopathic treatment" group and the combination of the two "specific osteopathic (sham) treatment" and "no treatment" groups.

The final composite endpoint (at M6) for chest and back pain will be compared using a linear mixed model with random intercept at the individual patient level in the context of Mixed Model for Repeated Measurements (MMR). This type of model can take into account the correlation of data for the same patient. Bilateral tests will be made at a 5% level.

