# 1. Objectives of the study

### 1.1 Primary objective

The primary objective is to assess the impact of osteopathic treatment on back-chest pain in adult patients with cystic fibrosis.

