## 2. Trial Design

MUCOSTEO is a randomized controlled multicenter study with three parallel arms of a total duration of 24 months (duration of participation: 6 months).

Eligible patients for this study are patients with cystic fibrosis and with chest, neck and / or back pain. After obtaining consent, patients will be randomized into 3 groups: a group receiving a general osteopathic treatment, a group receiving a specific osteopathic treatment (sham treatment) and an untreated group.

The treatment allocation will be done through a centralized randomization at URC (Clinical trial Unit), from a list of block randomization. Patient and physician investigator will be unaware of the allocation of patients in groups 1 and 2. Only the osteopathic practitioner will know the result of randomization.

After the initial visit during which randomization occurs, patients randomized in groups 1 and 2 will be monitored every month until M6 by the osteopathic practitioner. Patients in all three groups will be reviewed at M3 and M6 to collect evaluation criteria including assessment of pain, quality of life questionnaires and osteopathic assessment.

|  | **M0** | **M1** | **M2** | **M3** | **M4** | **M5** | **M6** |
| --- | --- | --- | --- | --- | --- | --- | --- |
| Inclusion /signature of consent | X |  |  |  |  |  |  |
| Randomization | X |  |  |  |  |  |  |
| Evaluation of pain | X |  |  | X |  |  | X |
| Quality of life questionnaire | X |  |  | X |  |  | X |
| Clinical exam | X |  |  | X |  |  | X |
| PFT (FEV1) | X |  |  | X |  |  | X |
| concomitant therapies (including analgesics) | X |  |  | X |  |  | X |
| Osteopathic evaluation | X |  |  | X |  |  | X |
| General (group 1) or specific (group 2) osteopathic treatment | X | X | X | X | X | X |  |
| Adverse events |  | X | X | X | X | X | X |

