### 6.3.4 Secondary analyses

For comparison, the results for the primary endpoint will also be given for the comparison of the "general osteopathic treatment group" vs. the "specific osteopathic treatment", and the "general osteopathic treatment group" vs. the "no treatment group". Bilateral tests will be realized at a 1.33% level (instead of 5%) in order to take into account the multiplicity induced by these two sensitivity analyses.

The final composite criteria (at M6) for neck and trapezius pain, headache and the 4 studied scores of quality of life (physical functioning, energy/well-being, body image, respiratory symptoms) will be analyzed using the same strategy as for the primary endpoint.

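### The primary test mixes the effect of general osteopathy beyond sham with half of any sham-versus-untreated difference, so a positive result alone does not show an effect beyond sham

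*Combined protocol and SAP*

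**What the plan says.** The primary objective (section 1.1) is to "assess the impact of osteopathic treatment on back-chest pain in adult patients with cystic fibrosis". Patients are randomised to general osteopathy, to a specific osteopathic treatment that serves as sham, or to no treatment. Section 6.2 plans 16, 8 and 8 patients.

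Section 2 describes masking for two of the three groups only: "Patient and physician investigator will be unaware of the allocation of patients in groups 1 and 2". Contact differs in the same way: "patients randomized in groups 1 and 2 will be monitored every month until M6 by the osteopathic practitioner". The schedule in section 2 gives groups 1 and 2 a treatment session at M0 and at each month to M5. Group 3 has none and is reviewed at M3 and M6.

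Both halves of the primary endpoint (section 6.1.1) come from the patient: a 0 to 10 pain rating for the past month, and "The number of days in the month when the patient experienced chest back pain", rescaled to 0 to 10.

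Section 6.3.3 makes the primary comparison general osteopathy against "the combination of the two 'specific osteopathic (sham) treatment' and 'no treatment' groups", two-sided at 5%. Section 6.2 bases the 80% power statement on that same comparison. Section 6.3.4 adds general versus sham and general versus untreated on the primary endpoint, each at 1.33%, and treats them as sensitivity analyses. No section gives a reason for pooling the two control groups or says how to read a positive primary test if general versus sham is not significant.

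**The concern.** A sham arm is there to remove expectation, attention and contact with the practitioner from the comparison. General versus sham does that. Pooling sham patients with patients who know that they receive nothing brings part of it back, on an endpoint that the patient rates. The primary estimate then has two components that it cannot separate.

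What is at stake is the reading of the headline result. The pooled test is the only one at 5% and the only one that the sample size supports. If it is positive and general versus sham is not, the plan does not say which result carries the conclusion.

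**Working it through.** **Inputs.** Group sizes of 16, 8 and 8, a difference of about 1 SD and 80% power (section 6.2); two-sided 5% for the primary test (section 6.3.3); 1.33% for the pairwise tests (section 6.3.4). Assumptions: equal SD in all arms, no dropout, and a single comparison at M6, because the covariates of the mixed model are not specified. Differences are in SDs of the endpoint; positive means less pain.

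**1. The plan's own figure.** For 16 versus 16 at 1 SD, the standard error is √(1/16 + 1/16) = 0.354. Power is Φ(1/0.354 − 1.960) = Φ(0.868) = 80.7%; the noncentral t gives 78.1%. The stated 80% is reproduced.

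**2. What the contrast estimates.** With 8 sham and 8 untreated patients, the pooled control mean is ½ sham + ½ untreated. Hence

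general − pooled = (general − sham) + ½ (sham − untreated).

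Write e for general − sham and s for sham − untreated. The expected difference is e + s/2. An expected difference of 0.75 SD arises from e = 0.75 and s = 0, from e = 0.5 and s = 0.5, or from e = 0 and s = 1.5. The pooled test cannot tell these apart.

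**3. No effect beyond sham (e = 0).** The documents give no value for s, so it is an assumed range. Simulated t tests, 100,000 or more trials per setting:

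| s (SD) | Expected pooled difference, s/2 | Pooled test significant, favouring general | Either direction |
|---|---|---|---|
| 0 | 0 | 2.5% | 5.0% |
| 0.25 | 0.125 | 5.3% | 6.3% |
| 0.5 | 0.25 | 9.5% | 9.9% |
| 0.8 | 0.40 | 17.3% | 17.4% |
| 1.0 | 0.50 | 23.7% | 23.8% |

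The benchmark for the third column is 2.5%. In the same scenarios general versus sham stays at about 2.5% in favour when tested at 5%, and about 0.7% when tested at 1.33%.

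**4. Power of general versus sham as planned.** For 16 versus 8 the standard error is √(1/16 + 1/8) = 0.433, so 1 SD is 2.309 standard errors.
- At 1.33% (critical value 2.475): Φ(2.309 − 2.475) = 43.4%; two-group t test 37.2%; three-group model with 29 degrees of freedom 38.7%.
- At 5%: Φ(2.309 − 1.960) = 63.7%; two-group t test 59.8%; three-group model 60.7%.

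**5. Effect of the proposed sequence.** With a true 1 SD effect over both controls (e = 1, s = 0), the pooled contrast and general versus sham are both significant in 58.6% of trials. With e = 0, both are significant in favour of general osteopathy in at most about 2.5% of trials for every s in the table.

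The three-level factor alone does not protect the pooled contrast. It takes the sham-untreated gap out of the residual variance, so the pooled test is positive slightly more often when e = 0: 10.1%, 19.3% and 27.7% at s = 0.5, 0.8 and 1.0, against 9.5%, 17.3% and 23.7% with two-group coding. The protection comes from the second step.

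**The case against.** The strongest reply is that the documents are consistent and the isolating comparison is already planned. Section 1.1 does not define the objective as an effect beyond sham, section 6.2 openly powers the trial against both control groups together, and section 6.3.4 pre-specifies general versus sham on the primary endpoint at a reduced level. All of this stands. A reader might infer that the trial cannot show that osteopathic treatment works; the documents do not support that. The limitation belongs to the pooled test read as evidence beyond sham.

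A reader might also infer that a sham response will by itself make the primary test positive. It can, but even at an assumed gap of 1 SD about three trials in four would not be positive for this reason, and at 0.25 SD the chance is about 5%.

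Section 6.2 calls this a pilot in a rare disease. That bears on the number of patients. It does not settle which contrast should carry the conclusion, and the same section claims 80% power to demonstrate a difference.

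A pragmatic reading of the pooled contrast, package of care against a mix of sham and no care, is possible. No section states it, but a correctly labelled result could still be reported that way.

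**Conclusion.** The point holds as a matter of what the primary test can support. The term ½ (sham − untreated) follows from the 8 and 8 allocation and needs no assumption about its size. Adjustment for baseline or repeated measures would change the percentages but would not remove that term.

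The error rates do rest on an assumption: gaps of 0.25 to 1.0 SD have no basis in the documents and are shown only as a range. Over that range the chance of a favourable primary result without any effect beyond sham is about 5% to 24%, against 2.5%. The comparison that would settle the matter is planned, but with about 37% to 43% power at 1 SD and with no role in the conclusion.

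Unequal dropout between sham and untreated patients could shift the mix in a merged control group. The documents give no dropout rate and this was not quantified, so it is a minor remark and the point does not depend on it.

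**What to change.** Revise sections 6.3.3 and 6.3.4 as follows.

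- Fit group as a three-level factor in the mixed model.
- Test at M6 in fixed sequence, each step at two-sided 5% and only if the step before is significant: (1) general versus the equal-weight mean of sham and untreated; (2) general versus sham; (3) general versus untreated. Report all three with 95% confidence intervals whatever the outcome.
- State that a significant step 1 alone supports only a difference between general osteopathy and a mix of sham and no treatment, and that any claim of an effect beyond sham requires step 2.

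The sequence controls the error rate across the three tests of the primary endpoint at 5%, so the 1.33% level is not needed for them. The first contrast, the sample size and the randomisation stay as they are.

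The costs should be written into the plan. The claim beyond sham has about 58.6% power at 1 SD (steps 1 and 2 both significant), against about 78% for the pooled test. This is still more than the roughly 39% that general versus sham has at 1.33% in the three-group model. Step 1 remains as sensitive to a sham response as before, or slightly more so. General versus untreated, which is now tested unconditionally at 1.33%, would be tested only if step 2 succeeds.

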## 4. Data collection

**At enrollment:**

*For all patients*

- Patient's identification (first letter of first name and first letter of name)
- Sex
- Date of signature of consent
- Age at enrollment
- Randomization arm
- Verification of inclusion and non inclusion criteria
- Collecting medical history
- Clinical exam
  - Date of exam
  - Age
  - Height
  - Weight
  - Pulmonary Function tests (FVC, FEV1)
  - Pulmonary infections
  - Clinical observation (Respiratory tract, digestive tract, cardio-vascular system, neurological system, skin condition, general condition)
- Assessment of pain (mean VAS and number of days in the previous month):) for :
  - neck and trapezus pain
  - chest and back pain
  - Headache
- Other pain (location, VAS, start date, end date, medication)
- Taking analgesics, NSAIDs, muscle relaxants or antidepressants during the previous month (name, dose, route, start date, end date, note)
- Osteopathic assessment (assessed area, severity, major or specific somatic dysfunction)
- Self-administered questionnaire of quality of life, specific for cystic fibrosis
  - physical functioning
  - energy/well-being
  - body image
  - respiratory symptoms

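### The M6 comparison specifies no adjustment for the M0 composite, although M0 is collected in every patient; stating one would add precision and protect against chance imbalance at almost no cost.

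*Combined protocol and SAP*

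**What the plan says.** The primary model is described in section 6.3.3: "The final composite endpoint (at M6) for chest and back pain will be compared using a linear mixed model with random intercept". The model is placed in a repeated-measures framework, and the reason given is that it handles correlation within a patient. No fixed effects, covariates or response visits are listed. The test is two-sided: "Bilateral tests will be made at a 5% level". The contrast is general osteopathic treatment against the sham and untreated groups combined.

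The M0 value is available. The enrollment list in section 4, under the items for all patients, includes "Assessment of pain (mean VAS and number of days in the previous month" for chest and back pain, and the schedule in section 2 places pain evaluation at M0, M3 and M6. The only stated use of inclusion data is the per-group description in section 6.3.2, which rightly excludes baseline significance tests.

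Section 6.3.4 says that the neck, headache and quality-of-life endpoints "will be analyzed using the same strategy as for the primary endpoint", so whatever 6.3.3 leaves open is left open for them too.

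Section 6.2 gives the sizing: "Total number of patients planned: n = 32", "Number of patients receiving general osteopathic treatment (group 1): n=16", eight patients in each of the other two groups, and "80% power to demonstrate a difference of about one standard deviation of the mean VAS for pain".

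**The concern.** In a trial of 32 patients, the M0 value of the outcome is usually the most useful covariate available, and here it is already collected. The plan nevertheless brings it into no comparison. A reader may take the random intercept as dealing with baseline. It does not: it describes how a patient's visits are correlated, and whether the M6 contrast is adjusted depends on how M0 enters the mean model.

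Two things are at stake. The first is precision, if M0 and M6 are at least moderately correlated. The second is chance imbalance. Section 2 describes a block list and mentions no stratification by pain. Section 3 admits patients on pain at any one of several sites, or on analgesic use, so chest-back scores at M0 may run from very low upwards. If the groups happen to differ at M0, part of that difference carries into an unadjusted M6 comparison.

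**Working it through.** **Inputs.** From the plan: 16 v 16 for the main contrast (8 + 8 combined), 16 v 8 for each pairwise contrast in 6.3.4, two-sided 5%, and a difference of 1 SD. Assumed: the M0-M6 correlation ρ, which the documents do not give, shown over a range; a random-intercept covariance (the same correlation between any two visits); and 32 complete patients, since no dropout rate is stated. All results are in units of the outcome SD.

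**1. The plan's own figure.** The unadjusted standard error of the M6 difference is √(1/16 + 1/16) = 0.354. Power at 1 SD is 80.7% by the normal approximation and 78.1% by the t test with 30 df. The stated 80% is reproduced without any baseline adjustment.

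**2. Standard error of the treatment effect at M6 under models compatible with 6.3.3.**

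| Model | Formula | ρ = 0.3 | ρ = 0.5 | ρ = 0.7 |
|---|---|---|---|---|
| M3 and M6 as responses, free group-by-visit means, no M0 | 0.354 | 0.354 | 0.354 | 0.354 |
| M0, M3, M6 as responses, free group-by-visit means, M6 contrast | 0.354 | 0.354 | 0.354 | 0.354 |
| Same model, change from M0 to M6 | 0.354 × √(2(1 − ρ)) | 0.418 | 0.354 | 0.274 |
| M0 as covariate, or M0 as response with a common mean | 0.354 × √(1 − ρ²) | 0.337 | 0.306 | 0.252 |

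The first two rows show that the random intercept alone leaves the M6 contrast unadjusted. The last row is the smallest at each ρ.

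**3. Power at 1 SD with M0 adjustment.** This uses the t test with 29 df. The standard error from the last row is multiplied by √(1 + 1/28) = 1.018 to allow for estimating the M0 slope.

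| ρ | Power, adjusted | Power, unadjusted |
|---|---|---|
| 0.1 | 77.0% | 78.1% |
| 0.2 | 78.3% | 78.1% |
| 0.3 | 80.4% | 78.1% |
| 0.5 | 87.3% | 78.1% |
| 0.7 | 96.4% | 78.1% |

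The difference detectable with 80% power is 1.02 SD unadjusted, and 0.99, 0.90 or 0.74 SD adjusted at ρ = 0.3, 0.5 or 0.7.

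**4. Chance imbalance at M0.**

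- 16 v 16: the SD of the difference in M0 means is 0.354, so P(|difference| > 0.5 SD) = 2 × [1 − Φ(0.5/0.354)] = 15.7%.
- 16 v 8: the SD is √(1/16 + 1/8) = 0.433, so the probability is 2 × [1 − Φ(0.5/0.433)] = 24.8%.

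**5. What an imbalance does.** A 0.5 SD imbalance shifts the unadjusted M6 difference by 0.5 × ρ = 0.15, 0.25 or 0.35 SD at ρ = 0.3, 0.5 or 0.7. Given that imbalance and no treatment effect, the M6 difference has mean 0.5ρ and SD 0.354 × √(1 − ρ²). The chance that it falls outside ±1.96 × 0.354 is 6.0%, 7.5% or 8.7%. Averaged over all randomisations the figure is 5%.

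**The case against.** The strongest reply is that 6.3.3 is silent and does not exclude M0. It lists no fixed effects at all, and a repeated-measures model with a common M0 mean fits the text and is as precise as a covariate. That stands. A reader might infer that the sponsor decided against baseline adjustment; the documents do not support this. They show only that no adjustment is specified. The silence still matters: the models in step 2 give different estimates and standard errors, and the text does not choose among them before the data are seen.

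The second reply is that the benefit depends on an unknown correlation between visits six months apart. That also stands. At 0.2 or below there is nothing to gain, and at 0.1 about one point of power is lost. The possible loss is small, however, and the possible gain is large.

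The third reply is that randomisation already protects validity and that the planned power does not rely on adjustment. Both statements are correct. A reader might infer that the planned comparison is biased, that its type I error is inflated, or that the sample size is wrong. None of these follows: the estimate is unbiased on average, the overall 5% level holds, and the 80% in 6.2 is reproduced. Nor is a large imbalance likely at the 0.5 SD threshold (16% for 16 v 16), and it carries over only in proportion to ρ.

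**Conclusion.** The point holds as a matter of precision and protection against chance imbalance. Section 6.3.3 specifies no use of an M0 value that every patient provides, and a random intercept alone does not supply the adjustment. Compared with the unadjusted M6 contrast, the gain in power at 1 SD is about 2, 9 or 18 points at ρ = 0.3, 0.5 or 0.7 (80.4, 87.3 or 96.4 less 78.1), and nil at about 0.2. These sizes rest on the assumed ρ, equal correlation between visits, and complete data on all 32 patients. The change is worth making, but nothing stated in the plan is invalidated without it.

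**What to change.** State in 6.3.3 that:

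- the responses are the M3 and M6 composites;
- the fixed effects are group, visit, group-by-visit and the M0 composite, with M0-by-visit optional;
- the group contrast at M6 is the primary estimate.

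An equivalent choice is M0, M3 and M6 as responses with the M0 mean held common across groups. One of the two should be named before the data are seen.

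In 6.3.4, apply the same model to the pairwise comparisons and to neck pain, headache and quality of life, each with its own M0 value. The schedule already collects these at M0.

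The cost is a few lines of SAP text and one or two degrees of freedom. No new data or visits are needed, and the sample size does not change. A side benefit is that the missing-at-random assumption in 6.3.5 becomes easier to defend, because missingness may then depend on M0 pain.

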## 3. Study Population

**Inclusion criteria:**

- Diagnosis of cystic fibrosis (positive sweat test and/or two CFTR disease-causing mutations)
- Age older than 18
- Patient with chest, neck or back pain (VAS> 2 or use of analgesics in the month before enrollment)
- Signature of consent
- Health insurance

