### 6.3.5 Handling missing data

No imputation strategy will be realized: the analysis being an analysis by mixed models, the parameters are estimated without bias in case of missing data under the assumption that these data are missing randomly.

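### The random-intercept primary model assumes one variance at all visits, which the documents do not support; an unstructured covariance with a stated degrees-of-freedom method would protect the M6 test

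*Combined protocol and SAP*

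**What the plan says.** Section 6.3.3 sets the target: "The final composite endpoint (at M6) for chest and back pain will be compared". The method is a "linear mixed model with random intercept at the individual patient level in the context of Mixed Model for Repeated Measurements (MMR", and the stated rationale is that "This type of model can take into account the correlation of data for the same patient". The test is two-sided: "Bilateral tests will be made at a 5% level". Section 6 does not give a residual covariance structure, a degrees-of-freedom method, a robust standard error or a fallback. It does not say whether M0 enters as an outcome or as a covariate.

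Pain is recorded at M0 (section 2 schedule and section 4), and "Patients in all three groups will be reviewed at M3 and M6 to collect evaluation criteria including assessment of pain". Section 6.2 gives "Total number of patients planned: n = 32", split 16, 8 and 8, so the main comparison is 16 v 16. Section 6.3.4 carries the same strategy over to the secondary endpoints. Section 6.3.5 relies on the mixed model in place of imputation, stating that "the parameters are estimated without bias in case of missing data under the assumption that these data are missing randomly".

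**The concern.** A random intercept with independent residuals is compound symmetry. A repeated-measures model of the MMRM type normally leaves the variances and correlations free across visits, so the label and the named device point to different models.

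Under compound symmetry, the standard error of the M6 difference comes from a variance averaged over all visits in the model, not from the M6 variance. If pain scores are more spread out at M6 than earlier, that standard error is too small and the test rejects too often. If they are less spread out, it is too large and power is lost. The level of the single primary test, its confidence interval, and the secondary tests built on the same model all depend on an equality that the plan neither states nor justifies. With 32 patients, the choice of degrees of freedom also has a visible effect.

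**Working it through.** **Inputs from the documents.** Visits M0, M3, M6; 16 v 16; two-sided 5%; target the M6 composite. **Assumptions.** All SDs and correlations (the documents give none), complete data, and a separate mean for each group at each visit.

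**1. The plan's own figure.** For a difference of 1 SD, n per group = 2 × (1.96 + 0.84)² = 15.7, so 16. Power at 16 v 16 is 80.7% by the normal formula and 78.1% by the t-test with 30 df. The sample-size statement in 6.2 reproduces and is not in question.

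**2. What the model implies.** With intercept variance σ_b² and residual variance σ_e², every visit has variance σ_b² + σ_e² and every pair of visits has covariance σ_b².

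**3. Standard error at M6.** The model uses √(mean of the three visit variances × 2/16). The true value is √(M6 variance × 2/16). Simulated type I error (20,000 to 40,000 trials per case) is in the last column; ranges reflect reference distributions with 30 and 60 df.

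| Assumed SD, M0/M3/M6 | Mean variance | Model SE | True SE | Ratio | Type I error |
| --- | --- | --- | --- | --- | --- |
| 1.9/2.0/2.1 | 12.02/3 = 4.01 | 0.708 | 0.742 | 0.95 | 6.0% |
| 1.8/2.0/2.2 | 12.08/3 = 4.03 | 0.709 | 0.778 | 0.91 | 7.3-7.4% |
| 1.5/2.0/2.5 | 12.50/3 = 4.17 | 0.722 | 0.884 | 0.82 | 10-11% |
| 2.5/2.2/2.0 | 15.09/3 = 5.03 | 0.793 | 0.707 | 1.12 | 2.7-3.0% |
| equal | common variance | same | same | 1.00 | about 5% |

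A hand check with 2{1 − Φ(1.96 × ratio)} agrees: 1.96 × 0.912 = 1.79 gives 7.4%, 1.96 × 0.816 = 1.60 gives 11.0%, and 1.96 × 1.121 = 2.20 gives 2.8%.

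As a more extreme conservative case, relative SDs of 1.3/1.0/0.7 give a ratio of √(1.06/0.49) = 1.47 and type I error of 0.5%. Power for a 1 SD difference at M6 falls from 78% to 46%.

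**4. Unequal correlation.** With equal SDs and correlation falling over time (0.7 for adjacent visits, 0.49 for M0 to M6), the M6 difference is unharmed: type I error stays at about 5%. If change from M0 were tested instead, the ratio would be √((1 − 0.63)/(1 − 0.49)) = 0.85 and type I error 9.5%.

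**5. M0 as a covariate, M3 and M6 as outcomes.** The restriction is now equal residual variance at M3 and M6 after adjustment for M0. With the equal-SD correlations of step 4, the residual variances are 1 − 0.7² = 0.51 and 1 − 0.49² = 0.76. The ratio is √(0.635/0.760) = 0.91 and type I error 7.5%. Relative SDs rising 0.7/1.0/1.3 gave 8.1-9.7%; SDs falling 1.3/1.0/0.7 gave 1.6-3.6%.

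**6. Unstructured covariance.** Type I error was 4.8-5.3% in every scenario, and power for 1 SD at M6 was about 78%.

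**7. Missing data.** A likelihood analysis predicts unobserved M6 values from observed visits through the modelled covariance. If that covariance is wrong, the M6 estimate can be biased even when data are missing at random. Dropout is not simulated here, so no size is attached to this.

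**The case against.** The strongest reply is that the plan is incomplete, not wrong. The text names a random intercept under an MMR label and does not exclude an additional residual structure. That stands: a reader who infers that the plan commits itself to compound symmetry goes further than the text. But the random intercept is the only device named, and an analyst following the text with default settings would fit exactly that model. The same wording cures either reading.

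A second tempting inference is that the entry rule makes M0 less variable than M6, so that the primary test is anti-conservative. The documents do not support this. The pain part of the criterion reads "VAS> 2 or use of analgesics in the month before enrollment", and it applies to chest, neck or back pain. A patient with neck pain only, or one who qualifies through analgesic use, can enter with a low chest-and-back score. The rule therefore does not clearly truncate the primary composite at M0, and the direction of any error is unknown.

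Third, the sizes rest on chosen SDs. Going from 1.5 to 2.5 is a 2.8-fold rise in variance (6.25/2.25) in six months, while the milder patterns give only 6-7%. This stands, and the figures should be read as a range under assumptions.

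Fourth, falling correlation does no harm to the M6 difference with complete data when all three visits are outcomes, and 6.3.3 does not mention change from M0. This also stands.

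Fifth, with complete balanced data the unstructured M6 contrast is simply the two-sample t-test, so its 5% level is no surprise. This is true. How an unstructured fit behaves with dropout in 32 patients, or in the 16 v 8 comparisons, has not been tested here. In a pilot study a parsimonious model is defensible, but its equal-variance assumption should then be stated.

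**Conclusion.** The concern holds in a limited form. On the standard reading of 6.3.3, the primary test assumes equal variance at every visit without support in the documents, and its standard error can be too small or too large. Under the assumed SDs of step 3, type I error runs from about 3% to 10-11%, with about 7% for a mild rise and about 5% if the variances are equal. These figures assume 16 v 16, complete data and separate means by group and visit.

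It does not follow that the 5% level will be exceeded, because the documents do not fix the direction. Nor does it follow that the treatment estimate is biased: with complete data the M6 point estimate is unaffected, and only the standard error, confidence interval and p-value are at risk. With missing data, the assurance in 6.3.5 is too strong as worded because it omits the condition that the covariance model be correct. This is an inexpensive improvement to the analysis plan, not a flaw in the trial's design.

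**What to change.** In 6.3.3:

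- Replace the random intercept with an unstructured within-patient covariance across visits: 3×3 with M0 as an outcome, or 2×2 for M3 and M6 with M0 as a covariate. Say which.
- Fit by REML with Kenward-Roger degrees of freedom, and specify SAS for this model, since 6.3.6 leaves open SAS and/or R.
- State that the test is the group difference at M6.
- Name heterogeneous compound symmetry as the fallback for non-convergence. It reduces six parameters to four in the three-visit version; with two visits it has the same three parameters as the unstructured form.

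Apply the same model to the 6.3.4 analyses. In 6.3.5, make the statement about unbiased estimation conditional on a correctly specified covariance as well as on missing at random.

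The cost is SAP wording, plus six covariance parameters (three in the two-visit version) where the random-intercept model has two. If compound symmetry were true, the loss would be a few degrees of freedom: in simulation, power for 1 SD at M6 was about 78% against about 80%.
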